## Abstract

**Background:**

Exercise has been shown to be beneficial for selected patients with heart failure, but questions remain over its effectiveness, cost-effectiveness and uptake in a real world setting. This paper describes the design, rationale and recruitment for a randomised controlled trial that will explore the effectiveness and uptake of a predominantly home-based exercise rehabilitation programme, as well as its cost-effectiveness and patient acceptability.

**Methods/design:**

Randomised controlled trial comparing specialist heart failure nurse care plus a nurse-led predominantly home-based exercise intervention against specialist heart failure nurse care alone in a multiethnic city population, served by two NHS Trusts and one primary care setting, in the United Kingdom.

169 English speaking patients with stable heart failure, defined as systolic impairment (ejection fraction ≤ 40%). with one or more hospital admissions with clinical heart failure or New York Heart Association (NYHA) II/III within previous 24-months were recruited.

Main outcome measures at 1 year: Minnesota Living with Heart Failure Questionnaire, incremental shuttle walk test, death or admission with heart failure or myocardial infarction, health care utilisation and costs. Interviews with purposive samples of patients to gain qualitative information about acceptability and adherence to exercise, views about their treatment, self-management of their heart failure and reasons why some patients declined to participate.

The records of 1639 patients managed by specialist heart failure services were screened, of which 997 (61%) were ineligible, due to ejection fraction>40%, current NYHA IV, no admission or NYHA II or more within the previous 2 years, or serious co-morbidities preventing physical activity. 642 patients were contacted: 289 (45%) declined to participate, 183 (39%) had an exclusion criterion and 169 (26%) agreed to randomisation.

**Discussion:**

Due to safety considerations for home-exercise less than half of patients treated by specialist heart failure services were eligible for the study. Many patients had co-morbidities preventing exercise and others had concerns about undertaking an exercise programme.

## Background

Heart failure is a major cause of morbidity and mortality in westernised societies and has a poor prognosis [1-3] Patients with heart failure (HF) suffer from a variety of symptoms, many of which are non-specific and often result in a poor quality of life[4], with decreased exercise capacity being the main factor restricting daily activity.

Heart failure management in the UK is currently undergoing major changes as a result of evidence showing the benefits of specialist nurses in reducing hospital readmissions[5,6] Specialist heart failure nurses funded both by the British Heart Foundation and by local primary care trusts are becoming part of the accepted standard of care for patients with heart failure. Specialist heart failure nurses do not currently provide structured exercise training[6,7].

### Effectiveness of exercise rehabilitation

Four systematic reviews have addressed the effectiveness of exercise training for patients with heart failure [8-11]. A qualitative review in 2002 concluded that short-term exercise training in selected sub-groups of patients led to short-term improvements on quality of life and had some physiological benefits[8]. However, it was noted that most trials were of short duration, small scale and focussed on physiological changes rather than morbidity and mortality. They also had included a patient profile that is not representative of typical heart failure patients, being younger, predominantly male and without co-morbidities[8].

A Cochrane review which included 1126 patients in 29 randomised controlled trials (RCT) concluded that for patients with New York Heart Association (NYHA) class II or III heart failure, exercise training improved exercise capacity and quality of life in the short-term. Improvements in exercise capacity were greater in programmes of greater intensity and longer duration[10]. One study[11] using an end point of combined events and mortality found no difference in combined events (death or adverse events) in the exercise group (OR 0.98; 95% CI 0.61 to 1.32) compared to the control group. There was a non-significant trend towards a reduction in mortality (OR 0.71; 95% CI 0.37 to 1.02, p = 0.06)[11]. The ExTraMATCH collaboration undertook an individual patient data meta-analysis by combining the datasets from eight RCTs with a total of 801 patients[9]. This had access to longer-term follow-up data than was available to the previous meta-analyses and showed an overall reduction in mortality in the patients who received the exercise intervention (hazard ratio 0.65; 95% CI 0.42 to 0.92)[9].

Only one trial has compared exercise training in patients with a control group receiving a specialist heart failure nurse intervention[12]. This evaluated an eight-week hospital rehabilitation programme including exercise and education followed by a 16 week community supervised exercise programme in patients referred to a specialist heart failure nurse and reported significant improvements at 24 week follow-up in the Minnesota Living with Heart Failure Questionnaire (MLwHF) and EuroQol scores, the New York Heart Association (NYHA) class and distance walked on the 6-minute walk between the rehabilitation and specialist heart failure nurse care only[12]. The exercise intervention occurred at the same time as medication was optimised and there was a higher proportion of patients in the intervention arm on beta-blockade, which may have accounted for some of the difference. In addition the rehabilitation programme included an educational component and was not solely exercise-based.

### Mechanism of action of exercise

The majority of trials of exercise in patients with heart failure have reported physiological improvements, which are mainly due to peripheral adaptations [13-18] There is some evidence that exercise increases cardiac stroke volume[16,19-21] and reduces cardiomegaly[16]. Exercise training has been shown to lower resting heart rate and improve myocardial perfusion[22]. The mechanisms of these actions include an improvement in the neurohormonal abnormalities seen in heart failure, enhanced vagal tone, and changes in skeletal muscle type and function [13]. Favourable changes in the indices of heart rate variability have been reported, which indicates improved autonomic control of heart rate and has been associated with improved survival[23]. However, trials of exercise interventions rarely report data on the extent to which medication use changed, which would have affected the outcomes.

### Type of exercise and settings

Current recommendations for exercise training are based on experiences from a limited number of randomised controlled trials that have enrolled highly selected patients. Questions remain about the optimal training modality and intensity[24] but current evidence suggests that training should include aerobic and resistance components. Peripheral muscles should be trained without a significant increase in cardiovascular stress[25], using intermittent exercise and/or sequential training.

Whilst the National Service Framework for coronary heart disease suggests that cardiac rehabilitation should be considered for patients with heart failure[26], it is rarely provided in the UK. Indeed, there are no published data on the uptake and acceptability of exercise-based rehabilitation for heart failure, but poor uptake post myocardial infarction (MI) occurs particularly in women, the elderly and patients from minority ethnic groups [27-31]. and the profile of patients with heart failure is older and includes more women than is the case for MI. Only one entirely home-based exercise intervention trial (20 patients in home arm) has been reported, with significant improvements in quality of life compared to patients receiving usual care[32].

### Rationale for Birmingham Rehabilitation Uptake Maximisation study for patients with congestive heart failure (BRUM-CHF) study

Whilst there are a number of very small trials of exercise interventions for patients with heart failure, questions remain about the effectiveness of exercise interventions outside specialist research units and in a representative patient population[24]. The follow-up period needed to be of sufficient duration to measure hospital admissions and mortality. In addition, apart from one trial[12], the reported trials of exercise rehabilitation were all compared to 'usual care'. The latter provided in these control arms is inferior to the specialist heart failure nurse intervention now offered as part of modern heart failure management programmes. There is also no evidence as to whether the improvements in quality of life and mortality in the exercise intervention groups in the published trials, are a result of physiological improvements or from the close clinical monitoring received alongside the exercise. It may also be that lifestyle and drug management advice was imparted with the exercise intervention and these improvements would now result from the specialist nurse intervention. The cost-effectiveness of exercise interventions has been addressed by only one study[33], which had usual care as the control group. This concluded that a long-term hospital-based exercise programme for people with stable heart failure was a cost-effective intervention[33].

The BRUM-CHF study proposes to establish the additional benefits of exercise rehabilitation compared to current care that includes specialist heart failure nurses. Given the potential problems with the capacity of the hospital service and uptake in a more elderly and debilitated population than other patients receiving cardiac rehabilitation for MI or revascularisation, it will be important to have information about effectiveness, uptake and compliance in a predominantly home-based setting.

### Study aim

The primary research question seeks to evaluate whether there are additional benefits from exercise rehabilitation over specialist heart failure nurse management and to establish the cost-effectiveness and patient acceptability of a predominantly home-based programme of exercise rehabilitation. In addition, the study will investigate the patient experience of heart failure and rehabilitation whilst attaining information about effectiveness, uptake and compliance of patients in a predominantly home-based setting.

## Methods/Design

BRUM-CHF is a randomised controlled trial of exercise rehabilitation in heart failure comparing specialist heart failure nurse care alone with specialist heart failure nurse care plus a structured exercise intervention.

Prior to commencement of the study, ethical approval was obtained from Sandwell and West Birmingham Local Research Ethics Committee (Reference number: 03/10/708).

Randomisation was performed centrally by computer at the Birmingham Cancer Clinical Trials Unit, University of Birmingham. When a patient was identified as eligible for the study, and had given written, informed consent to take part, the research nurse telephoned the trials unit. The Trials Unit randomly allocated patients, using the method of minimisation, stratified by (i) NYHA group, (ii) presence or absence of atrial fibrillation and (iii) hospital site.

In one arm patients continued with "usual" specialist heart failure nurse care. In the other arm patients continued with "usual" specialist heart failure nurse care combined with the exercise programme. The trial design is summarised in Figure 1. Patients who refused randomisation continued with their normal specialist nurse care.

### Population

The two NHS hospital Trusts and one Primary Care Trust from which patients were recruited are in the West Midlands, UK, covering a combined multiethnic population of approximately one million with a high incidence of heart disease. Recruited patients had left ventricular systolic dysfunction with an ejection fraction of 40% or less measured quantitatively, or classed qualitatively as 'moderate to severe impairment' on an echocardiogram, and were identified from three specialist heart failure nurse services. Recruitment took place over 19 months. Inclusion and exclusion criteria are summarised in Table 1.

Details of all patients referred to the specialist heart failure services were collected and suitability for study participation identified. Potentially eligible patients were contacted, invited to participate and assessed prior to randomisation by an incremental shuttle walk test (ISWT) to determine their suitability for exercise and to exclude patients with symptomatic ischaemia, cardiac arrhythmias or marked hypotension on exercise[34,35].

Baseline data collected prior to randomisation included the NYHA class, left ventricular systolic ejection fraction, demographic details (age, sex, ethnicity), disease history (admissions for heart failure) and past medical history, current medication, and outcomes (see below).

### Interventions

#### Specialist heart failure nurse care

"Usual care" is that provided by primary and secondary care with specialist heart failure nurse input. To ensure homogeneity of the intervention received, especially in relation to heart failure nurse input and receipt of optimal medical treatment, patients were recruited from those referred to the specialist heart failure clinic. The heart failure nurses had all undergone training from the British Heart Foundation.

#### Exercise intervention

The exercise group received "usual care" as described above, plus an exercise programme which commenced with three supervised exercise sessions to provide the patient with confidence and to plan an individualised exercise programme. This was followed by a home-based programme with home visits at 4, 10 and 20 weeks, telephone support at 6, 15 and 24 weeks and a manual.

The home programme was predominantly aerobic training based largely on progressive walking with self-completion activity logs. Exercise prescription was based upon the participant's baseline exercise tolerance as measured by the incremental shuttle walking test. Performance on this test correlates well with peak VO_2 _[34,36] An individually prescribed walking programme was identified from this test at a speed that corresponded to 70% of peak performance. During the first two weeks of rehabilitation the speed of walking was secured by the patient with the help of the rehabilitation team. Targets were set weekly for the duration and frequency of walks, which largely depended on an individual's baseline exercise capacity. The programme aimed for the patients to achieve 20 to 30 minutes of walking 5 times a week after 10 weeks of rehabilitation. This was monitored with home training diaries.

Strength training was low intensity, using the patient's own body weight for resistance. The focus of the strength training was both upper and lower limb. The "milk bottle regime" currently used in the rehabilitation programme in Leicester are used. Patients complete sets of up to 10 repetitions of 8 key exercise using milk bottles filled with gradually increasing volumes (thus weights) of water. Targets are set and level of difficulty assessed. Individual exercises are omitted in patients with particular needs or difficulties.

Specific support for the exercise intervention ceases after six months but patients are encouraged to continue to maintain their activity levels.

### Outcome measures

Follow-up by postal questionnaire and clinical assessment occurs at 6 months and by postal questionnaire at 1 year.

The primary outcome measure is the Minnesota Living with Heart Failure Questionnaire (MLwHF) Questionnaire[37]. Secondary outcome measures at 6 months are (i) composite of death or admission with heart failure or myocardial infarction, (ii) admission with heart failure, (iii) mortality (all-cause and vascular), (iv) EuroQol[38], (v) HADS[39], (vi) blood pressure, (vii) self-reported physical activity, and (viii) distance walked on the ISWT[36]. At 12 months the ISWT and blood pressure measurements are omitted.

Process measures to determine the comparability of intervention received from the specialist heart failure service included self-reported smoking cessation, salt reduction and alcohol intake. Uptake and adherence to the exercise intervention are assessed by (i) attendance at the hospital training sessions, and (ii) patient completed exercise diaries at 4, 10 and 20 weeks in the intervention group.

The study could not be double blind because of the nature of the intervention. To reduce the potential for bias in measuring outcomes in the questionnaires we used validated measurement tools and aimed for clinical follow-up to be undertaken by an individual who had not provided the rehabilitation support and was blinded to treatment allocation. Determination of secondary end-points (hospitalisation for heart failure and vascular mortality) was by an independent committee blinded to treatment allocation.

### Sample Size

The overall power of the trial was determined on the basis of the primary outcome – health related quality of life.

To detect a 10 point difference between the 'usual care' and supervised exercise group on the MLwHFQ (13 points at 1 year in Belardinelli)[22] at the 5% significance level with 80% power, 140 evaluable subjects at 1 year were needed. Allowing for 20% mortality and loss to follow-up a total of 168 recruits (84 per group) were needed.

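### Minor arithmetic error: the recruitment target adds 20% to 140 (168) instead of dividing by 0.8 (175), so 168 recruits with 20% loss leave about 134 evaluable patients, not 140

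*Protocol article*

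**What the plan says.** The calculation is in the Sample Size section of the protocol article and is based on the primary outcome, the Minnesota Living with Heart Failure Questionnaire.

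- Target effect: "To detect a 10 point difference between the 'usual care' and supervised exercise group on the MLwHFQ".
- Error rates and evaluable number: "at the 5% significance level with 80% power, 140 evaluable subjects at 1 year were needed".
- Inflation for attrition: "Allowing for 20% mortality and loss to follow-up a total of 168 recruits (84 per group) were needed".

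The section gives no standard deviation, does not say whether the test is one- or two-sided, and does not say whether the 140 assumes adjustment for baseline. The article gives no other attrition rate and no other basis for 168. The Abstract (Methods/design) reports the number recruited: "169 English speaking patients with stable heart failure".

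The Statistical analysis section plans least squares regression for continuous outcomes, with multivariate methods that take each patient's baseline measurement into account. It notes that this gives a more precise treatment estimate than raw outcomes or change scores.

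**The concern.** Deaths and losses to follow-up happen to recruited patients, so a 20% allowance is naturally a fraction of recruits. The number to recruit is then the evaluable number divided by the proportion retained. The article's target is what results from adding 20% to the evaluable number instead. That always gives too small a target, because 20% of the larger recruited number is more than 20% of the smaller evaluable number.

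The three stated figures (140 evaluable, 20% loss, 168 recruits) therefore cannot all be true. This is the power statement for the primary outcome, and recruitment ended at 169, in line with the stated target. Anyone who later reads the result against the planned power, or reuses the calculation for another trial, would take 168 as sufficient at 20% attrition. On the article's own figures it is not.

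**Working it through.** **Inputs (Sample Size section, except the last).** Evaluable patients needed: 140 (70 per group). Mortality and loss: 20%. Target: 168 (84 per group). Difference: 10 points. Significance level 5%, power 80%. Recruited: 169 (Abstract).

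**Step 1: reproduce the stated target.**
- 140 × (1 + 0.20) = 168, and 70 × 1.20 = 84 per group. Both match exactly.

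**Step 2: the inflation that fits a 20% loss among recruits.**
- n / (1 − d) = 140 / 0.80 = 175.
- For equal groups: 70 / 0.80 = 87.5, rounded up to 88 per group, or 176.
- Shortfall: 175 − 168 = 7 patients (4% of 175), or 8 with equal groups.

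**Step 3: what the stated target delivers.**
- 168 × 0.80 = 134.4 evaluable (67.2 per group).
- 169 × 0.80 = 135.2 evaluable.
- Largest loss that still leaves 140: 1 − 140/168 = 16.7%, or 1 − 140/169 = 17.2%.

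Steps 1 to 3 need no assumption beyond reading the 20% as a share of recruits.

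**Step 4: the size of the power loss.** This step needs assumptions that the article does not supply: a two-sided test, a normal approximation, and no gain from baseline adjustment beyond whatever is already in the 140.
- SD implied by the 140: 10 × √(70/2) / (1.960 + 0.842) = 59.16 / 2.802 = about 21.1.
- Power at 134.4 evaluable: Φ(2.802 × √(134.4/140) − 1.960) = Φ(0.785) = 78.4%.
- Power at 135.2 evaluable: Φ(2.802 × √(135.2/140) − 1.960) = Φ(0.793) = 78.6%.
- Difference detectable with 80% power at 134.4: 10 × √(140/134.4) = 10.2 points.

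The SD cancels from these power figures, which depend only on the ratio of 134.4 or 135.2 to 140. A one-sided test would hardly change them: Φ(2.486 × √(134.4/140) − 1.645) = Φ(0.791) = about 78.6%.

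**Step 5: how much baseline adjustment would offset.** Suppose the 140 came from an unadjusted comparison. Adjustment multiplies the residual variance by about 1 − r², where r is the correlation between baseline and 1-year scores.
- Needed to make 134.4 patients worth 140: 1 − r² = 134.4/140 = 0.96, so r² = 0.04 and r = 0.2.
- At r = 0.3: 134.4 / 0.91 = about 148 unadjusted patients.
- At r = 0.5: 134.4 / 0.75 = about 179 unadjusted patients.

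The article gives no value for r. These figures show the range only.

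**The case against.** The strongest case on the other side accepts the arithmetic and disputes its importance. The loss is about 1.5 percentage points of power and 0.2 points on the questionnaire. No estimate, test or endpoint changes. Results are to be reported with 95% confidence intervals, so a null finding would be judged from its interval. The planned baseline adjustment would restore the lost precision at a correlation of only about 0.2. All of this stands, and it is why the point is minor.

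A reader might infer something stronger: that the trial is underpowered, or that a null result could not be trusted. The article does not support that. The power figure rests on an unstated SD, an assumed two-sided test and no gain from adjustment. If the 140 was derived without adjustment, actual power at 20% loss could well exceed 80%. Equally, the article does not say that the 140 was unadjusted. If adjustment was already built in, the offset disappears. Power below 80% is therefore neither established nor ruled out.

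One could also read the 20% as a share of the evaluable number, since 28/140 = 20%. But 28 losses among 168 recruits is 16.7% attrition, which is not the ordinary meaning of an allowance for 20% mortality and loss. Nor can adjustment rescue the sentence: it may make fewer patients sufficient, but it does not turn 168 × 0.8 into 140, and the Sample Size section does not invoke it.

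**Conclusion.** The sentence is wrong as written, and the error is minor. The target was reached by multiplying by 1.2 when the stated loss calls for dividing by 0.8. It is 7 patients too low (8 for equal groups) and leaves about 134 evaluable patients at 20% loss, or about 135 from the 169 recruited. That much follows from the article's own figures. Power of 78–79% instead of 80% is conditional on the assumptions in the working, above all on no gain from baseline adjustment. What is established is a faulty inflation step in the sample-size statement, not a trial that lacks adequate power.

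**What to change.** Enrol no more patients and leave the design and analysis as they are. Correct the sample-size sentence along these lines: with 20% mortality and loss to follow-up, 168 recruits give about 134 evaluable patients and about 78% power for a 10-point difference, assuming a two-sided 5% test, an SD of about 21 and no gain from baseline adjustment; 140 evaluable patients at 20% loss would have required 175 recruits (176 for equal groups).

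If the authors prefer not to introduce an SD, the equivalent statement is that 168 recruits give 140 evaluable patients, and so 80% power, only up to about 16.7% loss. In that case they should keep the 20% as the original planning assumption and report 16.7% as what 168 can tolerate, so that the allowance does not look as if it had been chosen to fit.

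If the authors have the original calculation, adding its SD and whether it assumed baseline adjustment would settle how much power is really lost. The cost is one corrected sentence and a slightly less favourable power or attrition statement.
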